## Abstract

**Background:**

Traumatic childbirth experiences affect almost half of Australian women giving birth and can lead to significant mental health impacts, including postpartum depression, anxiety. and posttraumatic stress disorder (PTSD). Despite evidence supporting psychological interventions for birth trauma, there are prominent gaps in the accessibility of these treatments, particularly for postpartum women in regional or rural areas, who face long waitlists, geographical isolation, and high financial costs. Although narrative approaches hold promise for addressing birth-related trauma, no research study to date has specifically trialed a narrative-informed, group-based telehealth intervention in this space.

**Objective:**

This study aims to assess the acceptability and feasibility of a narrative-informed, group-based telehealth intervention for postpartum women in reducing the mental health impacts of having experienced a traumatic childbirth.

**Methods:**

This pilot feasibility trial with a waitlist control design evaluated a six-session narrative-informed, group-based intervention delivered weekly via telehealth to postpartum women who experienced a traumatic childbirth within the past 6 months. The intervention incorporated narrative therapy techniques, such as externalization, double-listening, and outsider witnessing. Participants from a specific catchment area of predominantly rural towns in New South Wales in Australia were randomly assigned to either an intervention group (IG) or a waitlist control group (WCG). Quantitative measures assessing mental health symptoms of postpartum depression (Edinburgh Postnatal Depression Scale [EPDS]), anxiety (Perinatal Anxiety Screening Scale [PASS]) and posttraumatic stress (City Birth Trauma Scale [City BiTS]) were administered prior to, in between, and at the end of treatment, and measures of client satisfaction (Client Satisfaction Questionnaire [CSQ-8]) and group cohesion (Group Cohesiveness Scale [GCS]) were administered on completion of the intervention.

**Results:**

The project was funded in March 2024. Recruitment was completed between July and August 2024. Eleven pretreatment sessions were held in August 2024. Of the 33 expressions of interest (EOIs) received by August 2024, 9 participants were recruited and randomized to the IG (n=4, 44.4%) and the WCG (n=5, 55.6%). The IG completed the six-session program between September and October 2024, with data collection finalized for pre-, mid-, and postintervention timepoints. The WCG began receiving the intervention mid-October 2024, with the final data collection in December 2024. Key feasibility and acceptability metrics include attendance rates, participant retention, and group cohesion scores. Data analysis is ongoing, with manuscript preparation planned for mid-late 2025.

**Conclusions:**

This study addresses a critical gap in evaluating scalable, accessible mental health interventions for birth trauma recovery. By using narrative approaches in a telehealth group format, this intervention directly responds to the barriers around accessibility and affordability highlighted in recent policy recommendations. Thus, findings from this pilot study could provide important directions in reducing the burden on perinatal mental health services in regional and rural Australia.

**Trial Registration:**

Australian New Zealand Clinical Trials Registry ANZCTR12624000460505p; https://www.anzctr.org.au/Trial/Registration/TrialReview.aspx?ACTRN=12624000460505p

**International Registered Report Identifier (IRRID):**

DERR1-10.2196/69051

## Introduction

### Background

Childbirth is a significant life event following on from pregnancy; however, almost half of the Australian birthing population (45.5%) reports having had a birth experience that they describe as traumatic and distressing [1]. Initially limited to physical injury during the birthing process, the current definition of a traumatic birth experience (interchangeably referred to as “birth trauma”) is “a woman’s experience of interactions and/or events directly related to childbirth that caused overwhelming distressing emotions and reactions, leading to short- and/or long-term negative impacts on a woman’s health and wellbeing” [2]. The risk of experiencing a traumatic childbirth increases when there is a history of previous trauma (including sexual trauma or birth trauma from a preceding birth experience); a history of mental health conditions; pre-existing disability; younger age; a lack of continuity of care (with respect to the availability of health professionals); having a lesbian, gay, bisexual, transgender, queer (or questioning), intersex, asexual, and other (LGBTQIA+) identity; living in a regional, rural, or remote area; and having a culturally or linguistically diverse background [3].

A wealth of literature links traumatic childbirth experiences or birth trauma to poorer mental health outcomes in postpartum women, including childbirth-related posttraumatic stress disorder (CB-PTSD), depression, and anxiety [4-9]. Further, the consequences of traumatic childbirth experiences have been shown to extend far beyond the immediate postpartum period and can also impact child outcomes [10]. Experiencing trauma symptoms postchildbirth has been linked to difficulties in breastfeeding [3,11] and, specifically, disruptions in mother-infant attachment and bonding [12-14]. These can have long-term adverse impacts on children’s socioemotional development [15,16] and long-term mental health [17], demonstrating the far-reaching impacts of traumatic childbirth experiences, if left unaddressed.

Given its widespread ramifications, the Parliament of New South Wales (NSW) formed a Select Committee in 2023 to conduct an inquiry into birth trauma. This is the first time in the world a parliamentary committee examined and reported on birth trauma. After reviewing over 4000 submissions from the community, the committee released a detailed report summarizing the submissions and hearings, as well as providing recommendations to reduce the likelihood of birth trauma and its adverse consequences [3]. Among various aspects pertaining to birth trauma, the report highlighted a dearth of adequate mental health services available for postpartum mothers, particularly in regional Australia, with long waitlists to see psychologists and expensive out-of-pocket costs for new parents [3]. This emphasized a critical need to offer accessible, cost-effective mental health services for postpartum mothers with traumatic childbirth experiences.

To address some of these barriers to accessing psychological interventions, such as long waitlists and higher costs, group-based interventions are a viable option for addressing mental health challenges in postpartum mothers, and have additional benefits of providing social support in the form of reducing feelings of isolation, having their feelings and experiences normalized and validated, and through modeling [18]. There has also been an increasing focus on telehealth interventions, necessitated by the COVID-19 pandemic. Research (including a systematic review and meta-analysis) has found that telehealth interventions are a feasible and effective option for supporting postpartum women with mental health diagnoses [19-21]. Taken together, group-based telehealth interventions have demonstrated increased attendance and comparable mental health outcomes to interventions delivered in person when treating mood and anxiety disorders in the general population [22,23] and have been successfully implemented to decrease symptoms of depression and posttraumatic stress in postpartum mothers as well [24]. This is significant, as psychological interventions that are group based and delivered via telehealth will greatly improve access to mental health services by overcoming established barriers to treatment, including affordability, availability, and convenience. For postpartum mothers in particular, such an intervention would further address additional barriers around time management, arranging for childcare, and needing to tend to their infants in an unfamiliar environment [25]. To date, no psychological intervention involving a telehealth group format for women with traumatic birth experiences has been studied.

Two systematic reviews [26,27] collated data from several studies that focused on the effectiveness of interventions to prevent CB-PTSD following birth trauma, ranging from primary prevention (antenatal education) to secondary prevention (hours to weeks following a traumatic childbirth) and tertiary prevention (when CB-PTSD is indicated). Most of the early intervention trials (ie, secondary prevention) focused on debriefing within 48-72 hours following birth or within 10 weeks postpartum, with no treatment effect on CB-PTSD [27]. The trauma-focused interventions reviewed included trauma-focused cognitive-behavior therapy (TF-CBT), individual or group based, predominantly with mothers whose infants were admitted to the neonatal intensive care unit or those with preterm infants, and eye movement desensitization reprocessing (EMDR) with women exhibiting symptoms of CB-PTSD [26,27]. A large proportion of these trauma-focused interventions demonstrated a positive treatment effect on CB-PTSD, with some of them reducing symptoms of postpartum depression or anxiety [26-28]. Specifically, for women at risk of or diagnosed with CB-PTSD, two Swedish studies trialed internet-based TF-CBT, with one study finding a positive treatment effect on CB-PTSD, depression, and anxiety [29] and the other finding no significant differences postintervention [30]. However, interventions such as TF-CBT and EMDR are required to be delivered by practitioners with specialized training in these modalities and therefore may be less available for postpartum mothers, particularly in rural areas. Further, these interventions have been predominantly trialed on women who are at risk of developing CB-PTSD or meet the diagnostic criteria for CB-PTSD versus women who report having experienced a traumatic childbirth, with or without symptoms of posttraumatic stress.

Women who report having had a traumatic birth experience frequently attribute their trauma to a lack or loss of control or sense of powerlessness [31], and birth storytelling has been found to be therapeutic for postpartum women, especially first-time mothers [32,33]. Therefore, a therapeutic approach incorporating narrative therapy techniques, such as externalizing the problems and reauthoring one’s story [34], which emphasizes self-empowerment, is likely to benefit this target population. Narrative therapy differs from other therapeutic modalities by explicitly acknowledging the social, cultural, and political contexts in which problems arise that ultimately shape the stories we tell ourselves [34]. As women’s childbirth experiences can be significantly impacted by sociocultural factors, political factors, and other practical concerns outside their control (eg, workforce shortages), a narrative-informed approach could be ideal in cultivating a strengths-based perspective on narratives. Narrative-informed interventions have been successfully used to address trauma delivered in group settings [35,36]. Linked to a narrative approach, a series of studies in Italy explored the use of a single instance of expressive writing within 48-96 hours postpartum, where women were asked to write about their labor and delivery experiences, focusing on their thoughts and feelings, the purpose of which was to develop a coherent narrative of their birth experience [37-39]. All studies indicated that expressive writing results in reduced psychological distress (depression and CB-PTSD) at 2-3 months postpartum [37-39].

Although curricula exist internationally for therapy groups for traumatic birth experiences [40], these have not been empirically evaluated. Therefore, this research will overcome this critical gap by assessing the acceptability and feasibility of a narrative-informed, group-based telehealth intervention for postpartum women in reducing the mental health impacts of having experienced a traumatic childbirth.

### Hypotheses/Research Question

Our first hypothesis is that a narrative-informed, group-based early intervention for postpartum women who have had a traumatic birth experience will be feasible and acceptable. Our second hypothesis is that the intervention will decrease symptoms of postpartum depression, postpartum anxiety, and/or postpartum post-traumatic stress disorder (PTSD) in women with traumatic birth experiences.

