### Sample Size

The study aimed to recruit 16 participants, which was deemed feasible within the project’s funding budget and timelines and is within the recommended size for group-based teletherapy [41]. As a pilot feasibility and acceptability study, should the study be deemed feasible and acceptable, the study findings may help inform estimates for sample size calculation for a larger trial. Consequently, no formal power calculation was performed for this study.

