### Data Analysis

#### Quantitative Data

All analyses will be based on the intention-to-treat principle. The quantitative data analyses will involve repeated-measures ANOVA entering the main effects for group, time, and group×time interaction, assuming α<.05 to denote a significant effect between the IG and the WCG for continuous study outcomes (City BiTS, EPDS, PASS). Assumption testing will examine normality using the Shapiro-Wilk test and sphericity using the Mauchley test of sphericity. Transformation and Huynh-Feldt correction will be applied, respectively, in the case of violation of these assumptions. The therapy process measures will be analyzed for between-group differences to determine the acceptability of the group intervention. As a feasibility and acceptability study, testing the proof of principle, our analyses will provide an estimate of mean (SD) change data and effect sizes to inform a larger trial in the future. The assessment of acceptability and feasibility postdelivery of the intervention, in both the IG and after the last session of the WCG, will afford the trial more quantitative data to identify aspects of the intervention that were perceived as beneficial and preferred.

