**Figure 1 figure1:**
[figure not shown]
Flowchart of the pilot trial procedure. IG: intervention group; WCG: waitlist control group.

To determine treatment acceptability, GCS-7 and CSQ-8 scores will be totaled for each participant, and a range of scores will be examined, including the central tendency score for each group. Higher scores will indicate greater treatment acceptability on both measures. Treatment feasibility will be determined by using attendance and retention metrics, with a threshold of 70% established as the criterion for feasibility drawn from recent research on virtual psychotherapy groups for postpartum mothers [24]. This threshold will apply to both individual participant attendance across all six sessions and overall retention, as measured by completion of postintervention measures across both groups. These predetermined benchmarks will provide clear criteria for determining whether the intervention warrants investigation in a larger trial.

The mental health outcome measures (EPDS, PASS, and City BiTS) will be scored according to the developer instructions. The last observation carried forward (LOCF) approach will be used to deal with any missing values, which involves replacing each missing value of a participant with the last observed value for that participant. The LOCF was chosen for its simplicity and frequent use in clinical trials [58]. As this is predominantly a feasibility and acceptability pilot study whose sample size is insufficiently powered to demonstrate statistically significant treatment effects, the LOCF was chosen over other more complex imputation methods that may not offer substantial benefits at this early stage. The average scores will be compared across the IG (who had these measures administered prior to, during, and after the intervention) and the WCG (who completed measures while they were on the waitlist, as well as after they received the intervention).

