### Study Limitations and Future Directions

This study has several limitations that warrant consideration. First, the statistical power for detecting significant changes in the mental health outcome measures is limited owing to the small sample size (n=9) in this pilot trial, and the use of single imputation methods (eg, LOCF) to deal with missing values is generally not recommended as it is based on the assumption that outcomes do not change if a participant does not fill in a specific measure [58]. However, the primary aim of this project is to examine the feasibility and acceptability of delivering such an intervention, not to comment on significant treatment effects. Further, as we are adopting an embedded mixed methods approach, it is anticipated that the qualitative data will provide a rich understanding of the processes facilitating change as a result of the intervention. If feasibility and acceptability are demonstrated in this study, then future research can look at using this intervention in large-scale trials with a priori power calculations to evaluate statistical significance. In this instance, multiple imputation methods would be recommended to deal with missing values in order to provide more robust estimates.

Second, it is possible that there has been a selection bias owing to recruitment through social media and health care professionals. Potential participants were to send in an EOI if they wished to participate in the study and could have had higher digital literacy, less perceived stigma, and greater help-seeking tendencies than other eligible persons who did not submit an EOI. Further, postpartum women outside of the geographical region under study, and those with infants older than 6 months of age, were not eligible to participate in this study, which meant that the intervention could not be offered even when they reached out (sent an EOI). Participants who were deemed ineligible were provided with alternate mental health support resource options that they could access. This recruitment strategy also potentially limited the cultural diversity in potential participants. Future research with larger trials could seek to deliberately recruit participants from culturally diverse backgrounds, which could speak to this intervention’s broader applicability.

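### Hypothesis 2 joins three symptom domains by and/or and each scale is tested at an unadjusted α<.05, which allows a significance claim that the protocol says its sample cannot support

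*Protocol article*

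**What the plan says.** - **Hypotheses/Research Question.** The second hypothesis is directional and concerns efficacy: "the intervention will decrease symptoms of postpartum depression, postpartum anxiety, and/or postpartum post-traumatic stress disorder (PTSD"). The three domains are joined by and/or, and no scale is given priority.
- **Data Analysis, Quantitative Data.** The model is a "repeated-measures ANOVA entering the main effects for group, time, and group×time interaction", with the criterion "assuming α<.05 to denote a significant effect between the IG and the WCG for continuous study outcomes (City BiTS, EPDS, PASS"). Two of these terms, group and group×time, compare the arms. The text does not say which one settles the hypothesis and states no adjustment across scales. The same paragraph says that mean (SD) change and effect sizes will be passed to a future larger trial.
- **Data Analysis, text after Figure 1.** The reason given for a simple imputation method is that the "sample size is insufficiently powered to demonstrate statistically significant treatment effects". The criterion for moving to a larger trial is the 70% attendance and retention benchmark.
- **Study Limitations and Future Directions.** The primary aim is feasibility and acceptability, "not to comment on significant treatment effects".
- **Abstract (Results) and Sample Size.** "9 participants were recruited and randomized to the IG (n=4, 44.4%) and the WCG (n=5, 55.6"). The target had been larger: "The study aimed to recruit 16 participants, which was deemed feasible within the project’s funding budget and timelines". No power calculation was made.

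**The concern.** A plan that fixes a threshold for declaring an effect, on three scales that can each satisfy the hypothesis, invites a declaration. The same plan says the sample cannot support one. If a single scale falls below .05, the authors can point to Hypothesis 2 and the stated criterion and report support for efficacy. The error rate behind that report is not 5%, and the accompanying effect size is large because only large observed effects can pass the threshold at this sample size. If no scale falls below .05, readers may take this as evidence of no effect, when the trial had little chance of detecting one. Both outcomes matter because the results are meant to inform a larger trial.

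**Working it through.** The protocol states no family-wise error rate, power or assumed effect size, so it has no figure to reproduce. Its only input of this kind is α = .05 per test.

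**Inputs.** Arms of 4 and 5 (Abstract, Results). Three scales at T1, T2 and T3 in both arms (Table 1). Two between-arm terms per scale (Quantitative Data). Assumed, because the protocol does not give them: correlation r between scales, varied from 0 to .9, and within-person correlation over time of .5.

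**1. False positives over three scales.** If the scales are independent, the chance of at least one is 1 − (1 − .05)³ = 14.3% for the three interaction tests. If the group terms also count there are six tests, and 1 − .95⁶ = 26.5%. For correlated scales, the planned 2-group × 3-time ANOVA was simulated under the null (60,000 runs per value of r):

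| r | Any of 3 interactions, either direction | Any of 3 interactions, in favor of IG | Any of 6 between-arm tests |
|---|---|---|---|
| 0 | 14.2% | 7.3% | 26.5% |
| .5 | 13.1% | 6.6% | 24.4% |
| .7 | 11.6% | 5.9% | 21.8% |
| .9 | 8.9% | 4.5% | 17.1% |

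The third column counts a significant interaction whose T1-to-T3 change favors the intervention, which is the direction in Hypothesis 2.

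**2. Smallest effect that can be significant.** For a simple two-group comparison, the minimum |d| is t(.975, 7 df) × √(1/4 + 1/5) = 2.365 × 0.671 = 1.59. Had the target of 16 been reached and split 8 v 8, it would be 2.145 × √(2/8) = 1.07. For the planned interaction test the error degrees of freedom are (9 − 2) × 2 = 14 and the critical F(2, 14) is 3.739. The smallest significant partial eta-squared is therefore (2 × 3.739)/(2 × 3.739 + 14) = 0.35.

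**3. Power and exaggeration.** These figures are for the simple 4 v 5 comparison at one time point, not for the planned ANOVA, whose power also depends on the within-person correlation. Power is from the noncentral t distribution. Exaggeration is the mean absolute raw difference among significant results divided by the true difference (400,000 runs).

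| True d | Power | Exaggeration if significant |
|---|---|---|
| 0.5 | 9.9% | 3.0 times |
| 0.8 | 17.9% | 2.1 times |
| 1.0 | 25.2% | 1.7 times |

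On Cohen's d the ratio at true d = 0.5 is larger (median 3.9 times), because small samples with a low SD are more likely to be significant.

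**4. Without selection.** If the effect size is reported whatever the p-value, the mean estimated d at true d = 0.5 is about 0.56. That is the ordinary small-sample bias of Cohen's d, not the inflation in step 3.

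**The case against.** The strongest reply is that this is an openly underpowered pilot whose efficacy hypothesis is secondary. The Discussion speaks of exploring potential impact, the Conclusion defers efficacy to adequately powered trials, and the decision on a larger trial rests on the 70% benchmarks, not on any p-value. All of that stands, and it limits the seriousness of the point. Handling of multiplicity may also sit in an analysis plan that is not shown, so its absence is not the complaint here.

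Four stronger readings are tempting, and the protocol does not support them:

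- *The protocol rules that one p<.05 meets Hypothesis 2.* It contains no such rule. The reading comes from putting the hypothesis and the analysis criterion together.
- *The protocol promises not to comment on significance at all.* The sentence in the limitations section describes the primary aim. A secondary exploratory test could coexist with it.
- *The chance of a false efficacy claim is 12 to 14% or more.* That range is two-sided and holds for low to moderate correlation. For a false decrease by the interaction test it is about half. A higher figure requires the group terms to count as well, which the text neither says nor rules out.
- *The effect sizes passed to the larger trial will be grossly inflated.* The plan promises them without a significance condition, and step 4 shows that unselected estimates do not carry this inflation.

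What the reply does not remove is the criterion itself. Admitting low power while keeping a threshold for declaring an effect leaves the inconsistency in place, and an analysis plan that added an adjustment would not resolve it.

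**Conclusion.** The point holds as an inconsistency in the published plan, of moderate weight. Hypothesis 2 and the α<.05 criterion together permit an efficacy claim on any one of three scales in nine women, and the protocol says elsewhere that the sample cannot support such a claim. Followed as written, the three non-directional interaction tests give at least one false positive about 14% of the time at r = 0, 13% at r = .5 and 12% at r = .7. The figure is about 24% at r = .5 if group main effects also count. A false decrease on at least one interaction test is about 6 to 7%. The correlations are assumptions, and above about .65 the three-test rate falls below 12%.

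An effect singled out because it was significant would overstate a true d of 0.5 about threefold on the raw difference. That rests on the simple two-group comparison and on the true effect being well below 1.6. At 10 to 18% power for d of 0.5 to 0.8, a non-significant result would say little.

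**What to change.** In Quantitative Data, delete the words "assuming α<.05 to denote a significant effect between the IG and the WCG"; the rest of the sentence can stand. Restate Hypothesis 2 as an exploratory estimation aim and remove the and/or. For all three scales, and whatever the p-value, report the IG−WCG difference in change from T1 to T3, or the baseline-adjusted difference at T3, with a 95% confidence interval. Make no efficacy claim. With 4 v 5, chance imbalance at baseline is likely, so an unadjusted T3 difference is not a good substitute.

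Do not name a lead scale now. The Abstract says final data collection was in December 2024 and analysis is ongoing, so a choice made at this stage would itself be open to the charge of selection.

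The cost is wording only. The sponsor gives up a significance claim that the protocol already says the sample cannot support. The intervals will be wide: for a simple two-group comparison the half-width is 2.365 × √(1/4 + 1/5) = 1.59 observed SDs. That width tells the planners of the larger trial how little the pilot fixes the effect size.
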